# INTRODUCTION AND RATIONALE

Non-Alcoholic Fatty Liver Disease (NAFLD) is the most common cause of liver dysfunction in the western world. It is strongly associated with obesity, insulin resistance, hypertension, and dyslipidemia and, as such, can be regarded as the hepatic component of the metabolic syndrome (de Alwis & Day, 2008; Younossi, 2019; Younossi et al., 2016). The current global prevalence of NAFLD has been estimated at 25 % of the adult population, however since obesity is reaching epidemic proportions worldwide, NAFLD is also expected to further increase in prevalence (Ekstedt et al., 2006; Younossi et al., 2016). Ethnic minorities show different predisposition to NAFLD. E.g. in the United States,  Hispanics predisposes to progressive NAFLD, whereas African background may be protective (Rich et al, 2018). Strikingly, to date no approved pharmacotherapy exists for NAFLD. NAFLD is attributable to high medical costs in society, which highlights the need for viable treatment options (Younossi, 2019).

NAFLD is defined as at least 5 % of hepatocytes presenting with steatosis (lipid accumulation), in absence of other hepatopathies, most importantly viral hepatitis, excessive alcohol consumption, or auto-immune or genetic liver diseases (Younossi et al., 2016). It is typically an asymptomatic illness, which explains why it in many cases can reach advanced stages before it is diagnosed. The diagnosis is typically made after routine health checks which identifies liver blood test abnormalities (NAFLD accounts for 60-90 % of such test results), however 80 % of patients with NAFLD have normal liver blood tests (de Alwis & Day, 2008). There appears to be no increase in mortality risk in patients with steatosis, which is often seen as rather benign, however patients with simple steatosis do suffer an increased risk of cardiovascular but not liver-related mortality (Bedossa, 2017; Ekstedt et al., 2006). The exact link between NAFLD and cardiovascular disease has not yet been clearly described (de Alwis & Day, 2008; Younossi et al., 2016). Moreover, longitudinal research indicates that most patients with NAFLD develop type 2 diabetes or impaired glucose tolerance over time due to increased adiposity, hence the collection of adipose tissue biopsies in this study (Ekstedt et al., 2006).

NAFLD covers a spectrum of liver diseases, ranging from simple steatosis, or NAFL, to its more progressive forms Non-Alcoholic Steatohepatitis (NASH), fibrosis, cirrhosis and hepatocellular carcinoma (HCC). Importantly, HCC can occur in the fibrotic state, i.e. before cirrhosis develops, indicating the toxic metabolic environment in NASH and setting NASH-HCC apart from e.g. HCC induced by viral hepatitis, which only occurs in the cirrhotic state (Bedossa, 2017; Friedman et al., 2018). NASH is defined as steatosis with hepatocyte injury, inflammation and fibrosis. In 10 years’ time, approximately 15 % of patients with simple steatosis will develop NASH (Chedid, 2017). Exact data for the Dutch population are lacking, but a study by Koehler et al. (2016) found presence of fibrosis assessed by transient elastography (TE) in 5.6 % of the general population over 45 years of age. It was associated with type 2 diabetes and steatosis. Currently the only possible method to discern between steatosis and steatohepatitis, and thus to determine the stage of NAFLD or NASH, is by histological examination which requires a liver biopsy. This is of high importance, since different stages have different prognoses and thus must be treated or managed differently (Bedossa, 2017; de Alwis & Day, 2008). Cirrhosis caused by NASH has become the most common cause of liver transplantations in the USA in 2018 (Younossi et al., 2016). Most patients have recurring steatosis within 4 years of a liver transplant, with 50% of that group progressing to NASH and fibrosis, and cases of recurrent cirrhosis have also been reported (de Alwis & Day, 2008; Gitto et al., 2018).

There are currently no pharmacological treatment options to treat NAFLD or to prevent its progression to NASH, NAFL-related fibrosis, or cirrhosis (Oseini & Sanyal, 2017; Ratziu, 2017). According to the European Association for the Study of the Liver (EASL), European Association for the Study of Diabetes (EASD), and the European Association for the Study of Obesity (EASO) (2016) the internationally recommended therapies include physical exercise and dietary modifications. Mainly, weight reduction through lifestyle interventions is the target to prevent NAFLD progression. It is stated in the guideline that 7-10 % weight reduction is recommended for NAFLD patients. Previously published intervention studies have investigated the effect of weight reduction through a combination of diet, exercise and behavioural interventions on the disease (Promrat et al., 2010; Vilar-Gomez et al., 2015). Results are still inconsistent whether weight loss is sufficient therapy in advanced stages of NASH whereas in steatosis even a small weight loss is beneficial for reducing liver fat and insulin resistance (Ratziu, 2017). However, weight reduction and its sustainability are more complicated in real-life clinical practice than seen in research intervention trials with intense guidance and follow-ups. Most of the obese patients who manage to lose weight successfully tend to regain most of it in the first 3 years. In addition to the difficulties related to weight management in health care, lifestyle interventions require a lot of investment and knowledge among health care professionals. Due to these matters it would be necessary to identify which specific lifestyle intervention would be the most effective to prevent the progression of NAFLD to increase efficacy, adherence and motivation.

Despite the fact that weight reduction is beneficial for the liver status, it has been indicated that hepatic fat can be reduced even without significant overall weight loss through lifestyle interventions (Katsagoni et al., 2017). This further confirms that lifestyle interventions are beneficial for NAFLD without directly targeting weight reduction. Indeed, physical exercise as a lifestyle intervention is seen to reduce liver fat without change in overall body weight (Keating et al., 2015). In longitudinal studies it has been shown that regular exercise minimizes the risk for developing NAFLD, and cardiorespiratory fitness is associated with changes in liver fat (Anderson et al., 2016; Kantartzis et al., 2009). In general, physical activity is a well-known lifestyle factor that influences overall health. Various epidemiological studies have shown the association between sedentary lifestyle and increased risk of diseases and mortality (Patterson et al., 2018). It is recommended for an adult to perform regularly either at least 150 minutes a week moderate-intensity or 75 minutes a week vigorous-intensity training or an appropriate combination of moderate- and vigorous-intensity aerobic activity with muscle-strengthening exercise for at least 2 times a week (US Department of Health and Human Services, 2018)

There are only a few randomized clinical intervention studies investigating the effect of physical exercise on NAFLD in humans all based on surrogate endpoints. In a 12-week randomized controlled trial with NAFLD subjects high-intensity aerobic interval (HII) training reduced (Mri based) liver fat and improved liver enzymes independent of weight change with decrease in fat mass (Hallsworth et al., 2015). Studies investigation aerobic exercise have found similar results with different duration of aerobic exercise intervention from 4 weeks up to 16 weeks (Johnson et al., 2009; Keating et al., 2015; Sullivan et al., 2011). Additionally, in a randomized clinical trial with 8-week intervention of resistance exercise (MRI based) liver fat was reduced without weight loss or change in body composition (Hallsworth et al., 2011). Another resistance exercise intervention with 12-week intervention (MRI based) liver fat content and body weight were reduced but there was no correlation between these parameters suggesting the improvement was not due to weight loss (Zelber-Sagi et al., 2014). After aerobic exercise levels of liver enzymes ALT and AST were decreased (Shamsoddini et al, 2016). Also, resistant training lowered the levels of these enzymes (Hajighasem et al., 2018; Zelber-Sagi et al., 2014). Although exercise is shown to reduce (MRI based) hepatic lipids in NAFLD patients, Houghton et al. (2017) demonstrated in a 12-week randomized clinical exercise trial that exercise does not have an influence on inflammatory markers or fibrosis in NASH patients. Altogether, although total training time, duration of sessions, frequency and exercise method vary greatly in previously published studies, for a precise conclusion it can be suggested that regardless of the type of the exercise intervention exercise alone is an effective method for reducing liver fat content either with or without change in body weight or body composition. However the organ specific regulation of each organ involved in metabolic fitness (including muscle, adipose tissue and liver) has not been studied at a molecular (biopsy) gene expression and histology level upon strenuous exercise in NAFLD subjects.

This is especially important as the liver seems to be the central orchestrator affected by exercise due to the major roles of the liver in metabolism. However, the mechanism behind the effect of exercise independent of body weight on hepatic fat is still unknown (Farzanegi et al., 2019). In general there is variation of the physiological response to exercise between different types of exercise. It is demonstrated that physiological response to exercise is seen in metabolism of lipids in adipose and skeletal muscle tissues. One reason for reduced lipids in the liver after regular exercise can be due to increased lipolysis and decreased lipogenesis (Trefts et al., 2015). It is also suggested that exercise has an effect on the inflammation due to increased lipid oxidation and then decreased lipid accumulation in liver mediated through exercise (Farzanegi et al., 2019; Trefts et al., 2015). However, the level of triglycerides and free fatty acids can be lowered only with weight decrease and that is why decrease in hepatic lipids without weight loss is not due to the transportation of lipids to the liver. Furthermore, exercise has a beneficial effect on insulin sensitivity in skeletal muscle and adipose tissues and also affects to glucose metabolism in the liver. Thus, it can be suggested that the effects of exercise on NAFLD is partly caused by the physiological response to exercise. However, performing a systems biology approach to dissect molecular pathways underlying the effect of exercise on hepatic lipids absent of weight loss in relation to other organs involved in metabolic fitness (muscle and adipose tissue) in NAFLD patients warrants more studies.

Previous studies have indicated alterations in the gut microbiota in patients with NAFLD, typically an overgrowth of bacteria in the small intestine, referred to as small intestinal bacterial overgrowth (SIBO). In addition to this NAFLD is associated with increased gut permeability, which correlates with the severity of steatosis (Miele et al., 2009; Wigg et al., 2001). Previous research has identified a causal relationship between NASH and the gut microbiota (Fischer et al., 2010). Changes in the gut microbiota can lead to worsening of steatosis and steatohepatitis in NASH mouse models, and these changes could be transmitted to wildtype mice (Henao-Mejia et al., 2012). In addition to this two observational studies found an increased abundance of Gammaproteobacteria in obese NASH patients compared to healthy controls, and a lower abundance of Bacteroidetes in subjects with NASH compared to subjects with steatosis (Mouzaki et al., 2013; Raman et al., 2013). Changes in gut microbial composition can be used to predict the development of choline deficiency-induced NAFLD, indicating the usefulness of this measure (Fischer et al., 2010).

Perhaps, these findings can be implemented in the relation to the effects of exercise, whether the mechanisms behind the effect of exercise on NAFLD is mediated through gut microbiota and related metabolites. The effects of exercise on gut microbiota have mainly been investigated in rodent models. Among human studies, a recent longitudinal study with obese and lean subjects tried to demonstrate the effect of exercise intervention on the modification of gut microbiota in obese and lean subjects (Allen et al., 2018). Another follow-up study with obese women showed also alterations in microbiota composition after endurance exercise intervention (Munukka et al., 2018). One recently published randomized crossover trial study with 33 subjects investigated whether a 5-week exercise intervention alters gut microbiota and how it is associated with the cardiometabolic phenotypes in elderly men (Taniguchi et al., 2018). In the exercise period compared to control period a significant decrease in the relative abundance of *Clostridium difficile* and a significant increase in *Oscillospira* were detected. The abundance of *Clostridium difficile* was correlated with AST, ALT among several other metabolic markers whereas *Oscillospira* was correlated with body weight, total cholesterol, HDL and HbA1c. In a mice model exercise-caused alterations in gut microbiota in donor mice were detected in recipient mice after five weeks of a colonization (Allen et al., 2018). The role of physical exercise on gut microbiota needs more randomized controlled trials for better understanding of the effects of exercise on gut microbiota.

Gut microbiome is strongly affected by the host including host’s genetics and ethnicity, but also it is affected by daily fluctuation of gut motility and transit time (Deschasaux, et al., 2018; Roager et al., 2016; Tottey et al., 2017). Strong inverse correlation is seen with defaecation patterns where increased stool frequency is correlated with decreased diversity (Hadizadeh et al., 2017). These changes might play a role also further in the metabolism of fermented carbohydrates and catabolised proteins in the colon affecting the whole body (Roager et al., 2016).  Furthermore, exercise has effect on gastric emptying (Horner, Schubert, Desbrow, Byrne, & King, 2015). The changes in defaecation patterns might be one of the explanatory factors of changes in the gut microbiota and metabolomes (Roager et al., 2016). Thus, the effects of gut motility require more studies to be able to address the underlying modulating factors upon interventions such as exercise interventions. Small bowel motility can be assessed by non-invasive dynamic MRI motility imaging which requires only a short imaging time (C. S. de Jonge, Smout, Nederveen, & Stoker, 2018; Catharina S de Jonge et al., 2018). As far as we know gut motility has not been previously studied in NAFLD patients upon exercise which might be essential when interpreting the effects of exercise on gut microbiome.

It has been estimated that gut bacteria in humans produce about 300 volatile organic compounds, and these bacterial products may be continuously delivered to the liver through the portal vein. The effect of this is largely unknown, however a previous study found that the role of gut microbiota in affecting metabolic pathways was important in cardiovascular disease (Knaapen et al., 2013). There have also been previous studies investigating the NAFLD specific metabolome. There are certain metabolic compounds found in feces that correlate with variations in the microbiome, specifically for NAFLD patients compared to lean controls (Raman et al., 2013) Previous studies have found that the liver and plasma metabolic profile in NAFLD correlates well, and plasma metabolomic profiling has been used to identify three distinct NAFLD patient subtypes (Alonso et al., 2017). In addition to this, several different studies have identified a very clear distinction in the NAFLD metabolome compared to healthy controls, some of these effects may be used to predict hepatic fat accumulation. Despite recent advances, reliable biomarkers are needed as an early diagnostic measure to be used by clinicians (Gitto et al., 2018).

The transcriptomic profile of adipose tissue in NAFLD is currently in the very early stages of being investigated. One study investigated adipose tissue transcriptome in adolescents, and found several uniquely regulated networks in normal, steatosis, and NASH samples (Sheldon et al., 2016) This suggests an important effect on the adipose transcriptome in NAFLD, however the driving forces of these effects are largely unknown. It is likely that the mechanisms can be further elucidated by investigating which genes vary upon HI exercise.

A few recent studies investigated the transcriptome in NAFLD liver samples, they identified several genes associated with cirrhosis and alcohol metabolism, and suggested potential functional pathways and networks that were affected during different stages of NAFLD. They found some pathway perturbations in both NAFL and NASH that were associated with lipid metabolism and cell cycle control (Almanza et al., 2018; Gerhard et al., 2018; Suppli et al., 2019; Ye & Liu, 2015; Zhu et al., 2016) Even specific sets of genes have been identified in subgroups of NAFLD that can aid in discerning between high- and low-risk NAFLD related mortality (Lou et al., 2017; Moylan et al., 2014; Starmann et al., 2012) Moreover several studies have been conducted to analyse the transcriptomic effect of diet on the NAFLD liver, however the effect of exercise on hepatic gene expression is largely unknown (de Wit, Afman, Mensink, & Müller, 2012; Sales et al., 2018). The gene expression changes in muscle tissue following exercise intervention in NAFLD patients has not been analysed previously, though it is known that exercise does affect the muscle transcriptome (Damas et al., 2018; Hinkley et al,2017; Keller et al., 2011; Lundberg et al., 2016). This intervention study and the analysis of muscle transcriptome can thus be of great importance in understanding the underlying molecular mechanisms of the exercise effect on NAFLD. Previous exercise intervention studies have found an effect on NAFLD, however there is scant evidence of the underlying mechanisms of this effect. In addition to this, there are scarce clinical studies that have investigated the effect of exercise on the microbiome in relation to NAFLD (Porras et al., 2018). This study will investigate the clinical effects of high intensity exercise on NAFLD, and explore whether these effects are related to changes in gut microbiota composition. In addition to this we will study whether potential changes in the gut microbiota can be used to monitor exercise progression and predict the prognosis of NAFLD. Finally, potential biomarkers will also be searched for by transcriptomic analyses of muscle, adipose, and liver tissue, and metabolomics analyses of blood and urine.

# OBJECTIVES

**Primary Objective:** to evaluate the clinical effect of high-intensity interval exercise on NAFLD liver histology and genes in relation to gut microbiome composition. To do this we will collect:

At baseline and endpoint:

- Anthropometrics (body weight, waist and hip circumference and body composition)
- Ergospirometry tests (VO2max)
- MRI and MRS scan of the abdomen to estimate liver fat content, fibrosis and abdominal fat depot assessed by MR modality, and also the liver fibrosis assessed by transient elastrography (FibroScan)
- Oral swab, Fecal and 24 h urine samples
- Free style Libre glucose monitoring (worn during 2 weeks)
- Blood samples (fasting plasma and DNA)
- (Ultra sound guided) Liver biopsy, muscle and adipose tissue biopsy for histology and gene expression
- REE
- Calf circumference

At mid-intervention:

- Body weight, waist and hip circumference
- Oral and fecal sample
- Blood sample (fasting)

At baseline:

- Height
- Ethnicity

At baseline, mid-intervention and endpoint:

- 4-day dietary intake list before the intervention and 5-day dietary lists before mid-intervention and endpoint

Through the entire intervention

- Physical activity questionnaire
- Objective physical activity monitoring

**Secondary Objective:** to analyse gut microbiota composition and identify novel biomarkers of high-intensity interval exercise effect on NAFLD liver genes progression. Also, we aim to study the relative contribution of each organ (liver/muscle and adipose tissue) in relation to gut microbiota composition and improvement in glucose metabolism upon exercise. To do this we will collect:

At baseline and endpoint:

- Fecal and 24 h urine samples
- Blood samples
- Liver, muscle and adipose tissue biopsy (for histology and gene expression)
- Gut motility

At mid-intervention:

- Fecal samples
- Blood samples

# STUDY DESIGN

This study is designed as an intervention study in which subjects will follow the 12-week exercise intervention. Subjects will receive instructions for a high-intensity aerobic interval training (HI) (described below). Dietary intake will remain unchanged. The first part of the study is conducted with 15 subjects. This is followed by an interim analysis and based on the results of this analysis, the intervention will be extended with another 15 subjects based on approval by the IRB. The study design is presented in figure 1.

Complementary study

Baseline

Mid-intervention

Final intervention

Interim analysis

Diagnosed NAFLD

(5.5 % > liver fat)

BMI < 40 kg/m^2^

18–70 years of age

n=15

Ergospirometry test

Anthropometrics

Food records

REE

Oral swab

Stool and urine samples

MRI and MRS

Blood samples

Liver, adipose tissue and muscle biopsies

Ergospirometry test

Anthropometrics

Food records

REE

Oral swab

Stool and urine samples

MRI and MRS

Blood samples

Liver, adipose tissue and muscle biopsies

Body weight

Food records

Oral swab

Stool samples

Blood samples

Exercise intervention – pilot study

Screening

Week 0

+/- 3 week

Identical to pilot study,

recruitment of

additional subjects

+/- 3 months

Continous glucose monitoring

Continous glucose monitoring

Week 12

+/- 3 week

Week 6

+/- 2 week

Figure 1 Overview of the study design with the main procedures that will be performed during the 12-week exercise intervention.

# STUDY POPULATION

## Population (base)

The 18-70-year-old subjects (n=15) will be recruited via advertisements from the outpatient clinics of the Amsterdam Medical Centre (AMC), and through newspaper advertisement.

## Inclusion criteria

In order to be eligible to participate in this study, a subject must meet all of the following criteria:

- Diagnosis of steatosis on transient elastography, conventional ultrasound, magnetic resonance imaging, computed tomography, liver biopsy, or identified as steatotic subject by fatty liver index (FLI) algorithm which is based on waist circumference, body mass index, and levels of triglyceride and γ-glutamyltransferase (Koehler et al. 2013).
- 18-70 years of age
- BMI < 40 kg/m^2^

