**SUMMARY**

**Rationale:** Non-Alcoholic Fatty Liver Disease (NAFLD) is the most common cause of liver dysfunction with a global prevalence of 25 % which is accompanied by increasing obesity and obesity related metabolic diseases. NAFLD is defined as at least 5 % of fat in hepatocytes in absence of other hepatopathies. It covers a spectrum of different disease stages varying from non-alcoholic fatty liver disease (NAFL) to an advanced stage of the disease called non-alcoholic steatohepatitis (NASH). NASH is defined as steatosis with hepatocyte injury, inflammation and fibrosis while in NAFL only lipid accumulation is detected. Hepatocellular carcinoma (HCC) can develop at the fibrotic stage before any sign of symptoms of liver dysfunction. The end stage of the disease is cirrhosis which is an increasing cause of liver transplantations in the western world. There are currently no pharmacological treatment options to treat NAFLD or to prevent its progression to NASH, NAFL-related fibrosis or cirrhosis. Internationally recommended therapies include lifestyle intervention modifications targeting weight loss. Nevertheless, lifestyle interventions require a lot of resources. Additionally, weight loss as a clinical intervention is rather unsustainable. Exercise has been demonstrated to reduce (MRI based) hepatic lipid content in NAFLD patients without overall weight loss. However, the mechanism behind the effect of exercise independently of body weight change is unclear. There is a strong link between gut microbiota and the development of NAFLD. Additionally, exercise modulates gut microbiota. Thus, it can be suggested that the effects of exercise on NAFLD may not only be mediated through a physiological response to the liver, but through the gut microbiota and related metabolites. This study aims to investigate the clinical effect of exercise on molecular mechanisms involved in NAFLD and explore both interaction and relative contribution of liver, subcutaneous adipose tissue and muscle histology and gene expression in relation to glucose metabolism and gut microbiome composition. In addition to this we will study whether potential changes in the gut microbiota can be used to monitor exercise progression and predict the prognosis of NAFLD. Finally, potential biomarkers will also be searched for by transcriptomic analyses of liver, muscle and adipose tissue, and metabolomic analyses of blood, feces and urine.

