**Objective**: We aim to study the effect of exercise on NAFLD (by analysing hepatic lipid content, liver histology, and gene expression). Furthermore, we aim to establish the role of exercise-mediated changes in gut microbiome in the reduction of severity of NAFLD and the relation with other metabolically involved organs including adipose tissue and muscle metabolism and glucose excursions. We thus aim to identify biomarkers of exercise effect on NAFLD state. These biomarkers comprise plasma and urine metabolites, gene expression of liver, muscle and adipose tissue, as well as gut microbial composition.

**Study design:** Intervention study.

**Study population:** In total 15 subjects aged 18-70 years of age with diagnosed NAFLD.

**Intervention (if applicable)**: High-intensity interval exercise training for 12 weeks.

**Main study parameters/endpoints:** The main study parameters are changes in NAFLD liver histology and gene expression in relation to oral and gut microbiota composition changes upon exercise. Second changes in other organs involved upon exercise driven metabolic fitness including subcutaneous adipose tissue and muscle gene expression (RNA-sequencing) and histology, in relation to glucose metabolism (freestyle libre) and metabolites in plasma and urine will be studied. Finally, the relative contribution to NAFLD and glucose metabolism of the different organs (liver, adipose tissue and muscle) upon exercise will be studied.

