**Nature and extent of the burden and risks associated with participation, benefit and group relatedness:**

This study is a continuation of our previous intervention studies aiming to study underlying mechanisms of gut microbiota in liver gene expression in NALFD-NASH subjects (MASH study 2013_207) and our study on the role of microbiota on muscle gene expression and glucose metabolism (APPETITE study 2014_084). Oral microbiota is studied by taking an oral swab of the upper front teeth rime in overnight fasted subjects that refrained from tooth brushing that morning (FATMED study 2016_117). Moreover, we currently are building a large prospective cohort of patients with NAFLD-NASH to follow the natural course of (liver biopsy proven) changes in NAFLD-NASH between baseline and after 5 years (2017_311). Participants will be recruited from our outpatient clinics. An ultrasound or transient electrography will be performed to establish hepatic steatosis, if they do not already have an existing diagnosis. All subjects will in total have six site study visits, and total 21 hours in 12 weeks. At each visit we will collect blood and fecal samples. In addition, body weight will be measured at each visit. Other anthropometrics including height and waist circumference will be screened at baseline. At the baseline (first) and endpoint (final) visit we will collect (ultrasound guided) liver, muscle and subcutaneous adipose tissue biopsies, and Magnetic Resonance Imaging (MRI) and Magnetic Resonance Spectroscopy (MRS) will be performed. During these two visits, bioelectrical impedance will be conducted to screen body composition and resting energy expenditure (REE) will be determined. Also, ergospirometry test will be performed to determine the intensity of the individually prescribed training program and the efficacy of the exercise intervention. Exercise habits will be assessed by a questionnaire for the entire 12-week intervention period. Additionally, an objective physical activity monitoring will be performed through the intervention. Subjects will also fill in online questionnaires regarding their food intake for one week prior to each visit. Glucose monitoring will be conducted for 4 weeks during the intervention, 2 weeks at the baseline and 2 weeks before the end of the intervention to screen the effect of the exercise on glucose metabolism.

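### Section 4.2 lets a subject enter on fatty liver index alone or on an undated diagnosis, which does not match Figure 1, and no rule removes a subject without current steatosis before biopsy

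*Protocol*

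**What the plan says.** The protocol describes entry in several places.

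- **Section 4.2 (Inclusion criteria)** accepts steatosis shown by any of five listed imaging or tissue methods, "or identified as steatotic subject by fatty liver index (FLI) algorithm which is based on waist circumference, body mass index" plus two blood values. The two routes are joined by an or. No FLI cut-off, minimum liver fat or date limit is given.
- **Section 3, Figure 1** shows diagnosed NAFLD with the bracketed condition "5.5 % > liver fat". No measurement method is attached to it.
- **Summary, study population:** "In total 15 subjects aged 18-70 years of age with diagnosed NAFLD".
- **Summary, burden and risks:** "An ultrasound or transient electrography will be performed to establish hepatic steatosis, if they do not already have an existing diagnosis".
- **Section 6.3.9** places FibroScan at the screening visit for subjects without a previous NAFLD diagnosis. Its Table 2 lists stiffness values for fibrosis stages and no steatosis value.
- **Disease definition:** the Summary says "NAFLD is defined as at least 5 % of fat in hepatocytes in absence of other hepatopathies"; section 1 says "NAFLD is defined as at least 5 % of hepatocytes presenting with steatosis".

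MRI/MRS and liver, muscle and fat biopsies are planned at baseline and endpoint. Section 6.3.13 waives the baseline liver biopsy if one was taken in the 12 months before screening.

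**The concern.** The criteria section is the text a site applies. Read as written, it can admit an obese subject with raised triglycerides whose liver fat has never been measured, or a subject whose steatosis was seen on an old scan and has since resolved. Neither need meet the protocol's own definition of NAFLD.

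Two things are at stake. First, a subject with little liver fat at week 0 has little room to improve, so each one pulls the mean change in liver fat and histological steatosis towards zero. The same is plausible for PNPLA3 expression, because section 4.4 builds its rationale on expression being twice as high in steatosis as in healthy obese subjects, and an FLI false positive may resemble the latter group. The first 15 subjects carry the interim analysis on which the extension depends, and with no control arm the dilution would be hard to see. Second, such a subject undergoes invasive liver sampling without having the disease under study.

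**Working it through.** **Step 1. Do the entry rules agree?** They do not.

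- Section 4.2 requires no liver measurement on the FLI route. Figure 1 attaches a liver-fat figure to the population.
- Figure 1 as printed reads as liver fat below 5.5%. That contradicts its own label of diagnosed NAFLD and the definitions of at least 5%.
- The definitions use different scales: fat in hepatocytes (Summary), share of hepatocytes with steatosis (section 1), and liver fat with no method (Figure 1).
- The 2013 source cited for FLI in section 4.2 is not in the reference list, so no cut-off can be traced from the document.
- Section 6.3.13 limits the age of a biopsy that replaces the baseline biopsy to 12 months. Section 4.2 puts no limit on the diagnosis that admits the subject.

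**Step 2. Does a later step close the gap?** None does.

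- Summary and section 6.3.9: imaging is planned where there is no existing diagnosis, but the consequence of a negative result is not stated, nor whether FLI positivity is an existing diagnosis.
- Section 4.3: absence of steatosis is not an exclusion.
- Section 6.4.1: it is not a withdrawal criterion.
- Sections 6.3.7 and 6.3.8: MRI/MRS measures liver fat in every subject, but no text uses it for eligibility.
- The Summary says what follows if the baseline biopsy shows NASH, but not if it shows no steatosis.

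**Step 3. Number of study liver biopsies for such a subject.** Two, or one if the 12-month waiver applies.

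**Step 4. Illustration of dilution.** The share p of enrolled subjects without steatosis is not in the protocol and is assumed here. Such subjects are further assumed to show zero change.

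- Mean effect is multiplied by (1 − p). Expected number among 15 is 15p. Chance of at least one is 1 − (1 − p)^15.
- At unchanged SD, the number needed for the same precision relative to the effect is multiplied by 1/(1 − p)².

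Power needs an SD. Section 4.4 gives 28 evaluable subjects for a 25% reduction (printed for PNPLA2, although the surrounding text concerns PNPLA3), two-sided alpha 0.05 and power 0.8, but no SD or proportions, so 28 cannot be reproduced from its stated inputs. Working backwards, a paired t-test with n = 28 has 80% power at a standardised change d = 0.549, that is, an SD of change of about 25/0.549 = 45.5% of baseline. Mixing in non-changers gives mean (1 − p)d and SD √(1 + p(1 − p)d²) in units of the within-group SD.

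| Assumed p | Expected of 15 | Chance of at least 1 of 15 | Mean reduction | 1/(1 − p)² | Power, n = 28 | Power, n = 15 |
|---|---|---|---|---|---|---|
| 0 | 0 | 0 | 25.0% | 1.00 | 0.80 | 0.51 |
| 10% | 1.5 | 79% | 22.5% | 1.23 | 0.70 | 0.42 |
| 20% | 3 | 96% | 20.0% | 1.56 | 0.59 | 0.34 |
| 30% | 4.5 | over 99% | 17.5% | 2.04 | 0.48 | 0.27 |

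The table shows sensitivity to p. It does not estimate p for this trial.

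**The case against.** The strongest reply is that the Summary already provides the missing check. Ultrasound and elastography are both on section 4.2's own list, so the Summary sentence is best read as a work-up step and not as a separate entry rule. On its natural reading, a subject flagged only by FLI has no diagnosis yet and would be scanned. This stands in part: it narrows the FLI route, so the text supports only that a subject without steatosis could be enrolled. It does not close the route, because FLI remains sufficient under section 4.2 and a negative scan has no stated consequence. It does nothing for an old diagnosis.

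Other stronger readings also fail. A reader might infer that every liver endpoint is diluted. Exercise may change hepatic gene expression without steatosis, and the wider transcriptome is a main endpoint (section 6.1.1), so dilution there is not shown; nor is it shown for fibrosis or inflammation. Liver fat below 5.5% is not zero, so the room to improve is small but not absent. Two biopsies is not universal, given the 12-month waiver. A reader might also take 5.5% to be an MRS threshold, but no text ties it to a method. Finally, the 10% to 30% share has no source in the protocol.

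**Conclusion.** The point holds as an inconsistency in the entry rules with a foreseeable consequence. Section 4.2 and Figure 1 do not agree, the sign in Figure 1 contradicts the figure's own label, and no rule removes a subject without current steatosis before biopsy. Such a subject could be enrolled and undergo one or two study liver biopsies.

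The effect on results is plausible for liver fat and histological steatosis, and probable for PNPLA3 expression given the two-fold contrast in section 4.4. Its size cannot be computed, because the protocol gives neither FLI's error rate nor the share of subjects entering by FLI or an old diagnosis. The tabulated losses rest on an assumed p, zero change in those subjects, and an SD back-solved from n = 28. Confidence is high for the textual conflict and lower for the consequences. The change should be made, since the confirming measurement is already planned for everyone.

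**What to change.** 1. Reconcile the Summary, section 3 (Figure 1), section 4.2 and section 6.3.9 into one eligibility definition, and correct the sign in Figure 1. The investigators set the threshold and the method.
2. Use FLI or an earlier diagnosis for pre-selection only.
3. Confirm current steatosis against that single definition on the baseline MRI/MRS already planned for every subject, read before the baseline biopsies. Subjects who do not meet it are screen failures.

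The cost is some screen failures after an MRI slot, and so slightly slower recruitment of the 15. The Summary puts MRI/MRS and the biopsies at the same baseline visit, so the scan must be read the same day or the visit split. The ±3 week window around week 0 in Figure 1 may leave room for that.
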